# STUDY SUMMARY

| Study Title | Effect of implementing an ambulance clinician delivered hypoglycaemia intervention (‘Hypos can strike twice’) on repeat ambulance calls, attendances and transportation to hospital: non-randomised stepped wedge and process evaluation |
| --- | --- |
| Study Design | Non-randomised stepped wedge design with mixed-methods process evaluation. |
| Study Participants | **Patients**  Young adults aged 16-17 years and adults aged 18 years+ with diabetes experiencing hypoglycaemia needing an ambulance service response.  **Clinicians**  Ambulance staff providing treatment and advice to people who have had a hypoglycaemic attack. |
| Eligibility Criteria | **Patients**  Young adults aged 16-17 years and adults aged 18 years+ with diabetes experiencing hypoglycaemia needing an ambulance service response. Hypoglycaemia for this study was identified as a ‘clinical impression’ of ‘hypoglycaemia’ or ‘diabetic problem’. Hypoglycaemia may also be identified according to ambulance guidelines^1^ as any blood glucose less than 4mmol/L.  **Clinicians**  Ambulance staff providing treatment and advice to people who have had a hypoglycaemic attack. |
| Planned Sample Size | Interviews: 10-15 staff and 10-15 patients, based on previous experience of the sample required to achieve theoretical saturation.  Survey: We will survey all front-line staff. The estimated sample size for patients is 447. |
| Study Duration | 12 months |
| Objectives | Aim: To evaluate the effect of implementing the ‘Hypo’s can strike twice’ intervention to patients with diabetes and hypoglycaemia attended by East Midlands Ambulance Service NHS Trust in the East Midlands region.  Objectives: To investigate the effect of implementing the ‘Hypo’s can strike twice’ on:   1. Repeat ambulance calls and attendances for hypoglycaemia; 2. Recorded referrals to an appropriate healthcare professional (e.g. GP, nurse); 3. Completed care bundle for hypoglycaemia (proportion of patients with all of blood glucose recorded before treatment, blood glucose recorded after treatment and treatment given for hypoglycaemia; 4. Costs of implementation ‘Hypo’s can strike twice’ intervention vs costs of health service resource use; 5. To conduct a process evaluation to explore how ‘Hypo’s can strike twice’ exerts its effects and can be scaled up if effective by understanding implementation, mechanisms of impact, and contextual factors using interviews and surveys. |

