# STUDY DESIGN

Non-randomised stepped wedge design with mixed methods process evaluation.

Work package (WP) 1 Stepped wedge: We will use routine anonymised data from routine call-and-dispatch and clinical records data from EMAS for 12 months before the intervention was first introduced (September 2017) to at least 6 months after the final step of the introduction in April 2019, i.e. October 2019. We will include call categories, timings, geographical location, together with demographic (age, sex) and clinical information, physiological measurements taken, treatments given, and whether the patient was referred to community services (general practitioner, community diabetes nurse or alternative) for their diabetes or transported to hospital by ambulance. Hypoglycaemia is recorded in electronic clinical records under ‘chief complaint’ or impression’ which will enable us to identify incidents of patients presenting with hypoglycaemia. Individual patients will be assigned a unique (non-personally identifiable) number in the anonymised dataset provided to the university which will enable us to identify repeat attendances for an individual patient.

WP2 Health economics: We will use a cost-consequences approach to estimate the costs of the intervention in relation to its effects. Total costs will be estimated, from an NHS perspective, using unit costs from NHS Reference Costs, Emergency Services Reference Costs, and other relevant costs, multiplied by resource units.

WP3 Survey: We will use a self-administered survey to understand implementation, mechanisms of impact, and contextual factors. We will use random sampling to select patients with hypoglycaemia who were attended stratified by geographical area, from the ambulance service user records and we will send them questionnaires by post (with a stamped addressed envelope for return to the University of Lincoln) or offer them the option to complete the questionnaire on-line, according to their preference. We will conduct an online survey to all front-line clinicians to assess attitudes, perceptions and behaviour towards the intervention including the booklet. We will also conduct a self-administered postal questionnaire to patients using a Patient Reported Experience Measure, previously developed and validated by [name] and colleagues^19 20^. The sample size calculation for the survey is included below.

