### Sampling

### Size of sample

WP1 and 2 Stepped wedge (non-randomised control design):

3 clusters at county level (1.Leicestershire+Northamptonshire; 2.Derbyshire+Nottinghamshire; 3.Lincolnshire) implementing intervention at each time step lasting around 3 months, so 12 data collection periods (one collection per cluster per time step).

Primary outcome: Proportion of repeat ambulance calls and attendances for hypoglycaemia within 14 days.

Significance level = 0.05

Intraclass coefficient = 0.1 (conservative estimate)

The number of hypo calls per time period (3 months) per county group was estimated from routine data from EMAS for years 2012-2017 (6 years).

| **County group** | **Frequency** | **Percentage** |
| --- | --- | --- |
| Leicestershire | 639,811 | 19.39 |
| Northamptonshire | 449,916 | 13.63 |
| Derbyshire | 662,745 | 20.08 |
| Nottinghamshire | 773,066 | 23.43 |
| Lincolnshire | 774,128 | 23.46 |
| Total | 3,299,972 | 100.00 |

Number of hypos expected every 3 months = 1% of attendances

Leicestershire Northamptonshire = (639811+449916)*0.01*(1/24) = 454

Derbyshire Nottinghamshire = (662745+773066)*0.01*(1/24) = 598

Lincolnshire = (774128)*0.01*(1/24) = 323

Proportion pre-intervention with a repeat attendance = 0.1

Power is fixed at 80%.

The detectable difference is a reduction of repeat attendances of 5% (i.e. from 10% to 5%).

WP3 Survey: We will survey all front-line staff. We will survey patients who received the intervention based on a response rate of 20% from a previously published study using the Ambulance Patient Reported Experience Measure.^19 20^ In this study the experience measure included 3 components AmbCallScore (mean 62.37, standard deviation 26.7), AmbCareScore (mean 85.6, standard deviation 16.4) and AmbLeaveScore (mean 73.77, standard deviation 21.6) Assuming the proportion of sample with the expected outcome: 0.50, margin of error: +/- 10.0%, confidence level: 95.0%, the estimated sample size required is 96. The estimate adjusted for a 20% response rate is 447. This means sampling from 447 we anticipate an estimate of each of the scores that is within 10% of the true value.

WP4 Qualitative; The qualitative sample of 10-15 staff and 10-15 patients is based on previous experience of the sample required to achieve theoretical saturation.

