**Process evaluation**

We will conduct a process evaluation using surveys and interviews of ambulance staff and patients to explore how ‘Hypo’s can strike twice’ exerts its effects and can be scaled up, if effective, by understanding implementation, mechanisms of impact, and contextual factors.

*Survey*

We will use a self-administered survey to understand implementation, mechanisms of impact, and contextual factors. We will use random sampling to select patients with hypoglycaemia who were attended, stratified by geographical area, from the ambulance service user records and we will send them questionnaires by post (with a stamped addressed envelope for return to the University of Lincoln) or offer them the option to complete the questionnaire on-line, according to their preference. We will conduct an online survey to all front-line clinicians to assess attitudes, perceptions and behaviour towards the intervention including the booklet. We will also conduct a self-administered postal questionnaire to patients using a Patient Reported Experience Measure^19 20^. We will survey all front-line staff and approximately 447 patients.

We will analyse the overall experience of both patients and ambulance staff, as well as use descriptive statistics and comparisons between responder groups (e.g. ambulance staff vs patients; paramedics vs emergency medical technicians), where appropriate.

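### Patient survey size of 447 does not follow from 96 completed questionnaires at a 20% response rate (that gives 480), and the precision sentence is not derived from the quoted SDs

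*Protocol*

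**What the plan says.** The Protocol, Size of sample (WP3 Survey), quotes a 20% response rate from an earlier study that used the same patient experience measure, with means and SDs for its three component scores. The calculation starts from a proportion ("Assuming the proportion of sample with the expected outcome: 0.50") and a "margin of error: +/- 10.0" percent at 95% confidence, and gives the result that "the estimated sample size required is 96". The response adjustment follows: "The estimate adjusted for a 20% response rate is 447". The paragraph closes with the claim that "we anticipate an estimate of each of the scores that is within 10% of the true value".

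The figure appears twice more. The Study Summary has "The estimated sample size for patients is 447", and the Process evaluation section has "We will survey all front-line staff and approximately 447 patients".

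On who is surveyed, Size of sample limits the survey to recipients of the intervention. Study Design describes the draw without that limit: "We will use random sampling to select patients with hypoglycaemia who were attended stratified by geographical area". The Process evaluation section uses nearly the same description.

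**The concern.** There are two faults in the derivation.

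First, 96, 20% and 447 cannot all stand as written. Dividing 96 by 0.20 does not give 447, and no other step is described. If 447 packs are posted and 20% come back, the returns fall short of the number that the same paragraph calls required.

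Second, the formula and the conclusion concern different quantities. The formula gives an absolute margin, in percentage points, for a proportion. The conclusion is about mean scores and a margin expressed as a percentage of the true value. The means and SDs that would support such a statement are quoted in the same paragraph but do not enter the calculation.

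At stake are the internal consistency of a stated sample size and a precision claim that a reader cannot trace. The survey belongs to the process evaluation, so the primary outcome is not affected.

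**Working it through.** Inputs, all from Size of sample (WP3): p = 0.50; d = 0.10; 95% confidence, z = 1.96; response rate 0.20; stated requirement 96; stated mailing 447; AmbCallScore mean 62.37, SD 26.7; AmbCareScore mean 85.6, SD 16.4; AmbLeaveScore mean 73.77, SD 21.6.

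**1. Required returns.** n = z² p(1 − p) / d² = 1.96² × 0.25 / 0.10² = 96.04. The plan's 96 reproduces.

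**2. Response adjustment.** 96 / 0.20 = 480. The stated 447 is 33 lower, and 480 is 7.4% above it. Rounding does not close the gap: rounding the requirement up to 97 moves further away (97 / 0.20 = 485).

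**3. What 447 mailings give.** 447 × 0.20 = 89.4 returns. Margin for p = 0.50: 1.96 × √(0.25 / 89.4) = 0.1036, so ±10.4 points. To get 96 returns from 447 mailings, the response rate would have to be 96 / 447 = 21.5%.

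**4. Could a finite-population correction explain 447?** With n = 96.04 / (1 + 95.04 / N):
- N = 1,280 gives 89.4 required returns, and 89.4 / 0.20 = 447.
- N = 1,375 (the 454 + 598 + 323 hypoglycaemia calls per three months in the same section) gives 89.8, and 89.8 / 0.20 = 449.

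This route comes close, but the protocol states neither a survey population nor a correction. The requirement would also then be about 89 or 90, not 96.

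**5. Precision for the scores.** Half-width = 1.96 × SD / √n.

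| Score | n = 96: points (% of mean) | n = 89: points (% of mean) | n for 10% of the mean | Mailings at 20% |
| --- | --- | --- | --- | --- |
| AmbCallScore | 5.3 (8.6%) | 5.5 (8.9%) | 71 | 355 |
| AmbCareScore | 3.3 (3.8%) | 3.4 (4.0%) | 15 | 75 |
| AmbLeaveScore | 4.3 (5.9%) | 4.5 (6.1%) | 33 | 165 |

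The fourth column is (1.96 × SD / (0.10 × mean))², rounded up. For AmbCallScore: (1.96 × 26.7 / 6.237)² = 70.4, so 71. Even the most demanding score needs fewer mailings (355) than the 447 planned.

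**The case against.** Four points can be made for the plan.

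*The precision promised for the scores is kept.* This stands. A reader might infer from the shortfall in returns that the stated precision is missed. The quoted SDs show otherwise: with about 89 returns all three half-widths are below 10% of the mean. Only the margin for a proportion slips, from 10.0 to 10.4 points.

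*Using p = 0.50 is a common conservative choice.* This stands in part. If the scores run from 0 to 100 (an assumption, since the range is not stated), their SD cannot exceed 50, so 96 returns bound the half-width at 1.96 × 50 / √96 = 10 points. That is a bound in points. As a percentage of the mean, 10 points is 16.0% of 62.37, 11.7% of 85.6 and 13.6% of 73.77. The proportion calculation therefore does not by itself deliver the closing sentence, although the SDs do.

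*An undocumented finite-population correction may lie behind 447.* This is plausible, because the call numbers in the same section give 449. If it was used, 447 mailings would give about ±10 points and 480 would be unnecessary. It cannot be confirmed, and it conflicts with the stated 96. It does belong among the possible repairs.

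*The sampling frame is not contradictory.* A reader might infer from Study Design that questionnaires will go to everyone attended between September 2017 and October 2019, so that most would reach people who were never offered the booklet. The protocol does not support that. Size of sample names recipients of the intervention, and the two descriptions of the draw merely leave the limit out. The dates describe the routine dataset used to identify potential participants, and nothing says that the survey draw ignores rollout. What remains is a wording point.

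**Conclusion.** The survey size is wrong as written: on the stated inputs it is 480, not 447, and 447 is repeated in two other places. With 447 mailings and 20% response, the plan should expect about 89 returns and ±10.4 points for a proportion of 0.50. The closing precision sentence does not follow from the proportion calculation, but it is true on the quoted SDs (half-widths of 8.9%, 4.0% and 6.1% of the means with 89 returns). This rests on the 20% response rate, on the SDs of the earlier study holding here, and on simple random sampling without a finite-population correction.

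It is a minor error of derivation and consistency in a descriptive survey. It does not make the survey inadequate for the scores, and it does not bear on the effectiveness analysis. The omitted restriction in the sampling descriptions is a secondary matter of wording and does not show that unexposed patients would be surveyed.

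**What to change.** Make 96, 20% and 447 agree in Size of sample, the Study Summary and the Process evaluation section, in one of three ways:
- change 447 to 480; or
- keep 447 and state about 89 expected returns and ±10.4 points for a proportion of 0.50; or
- if a finite-population correction was used, state the population and give the corrected required number in place of 96.

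Replace the closing sentence of the WP3 paragraph with the 95% half-widths from the quoted SDs: about 5.3, 3.3 and 4.3 points with 96 returns, or 5.5, 3.4 and 4.5 points with 89.

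In Study Design (WP3) and in the survey part of Process evaluation, repeat the restriction to recipients of the intervention that Size of sample already makes.

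The cost is 33 more postal packs if 480 is chosen. The other two options, the precision sentence and the sampling descriptions need only changes of wording.

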## RECRUITMENT

To identify potential participants, we will use routine anonymised data from routine call-and-dispatch and clinical records data from EMAS for 12 months before the intervention was first introduced (September 2017) to at least 6 months after the final step of the introduction in April 2019, i.e. October 2019. The data will be obtained and pseudo-anonymised by a member of the team at EMAS. The final dataset for this study will only be accessible to the Chief Investigator, the Clinical Database Manager, the Research Assistant(s), the Health Economist(s), and the Statistician(s).

Eligible ambulance staff members will receive an email, from a member of the team at EMAS, explaining the purpose of the study and what it will involve and inviting them to participate in the study. The email will also include a PIS and a link to the online survey. Participants will be asked to give their consent online, as part of the online questionnaire, and unless consenting to all statements of the consent form, they will not be able to continue to the questionnaire.

Members of the team at EMAS will send (by post) a study pack to eligible patients, including a study PIS, a consent form, a paper copy of the questionnaire and a pre-paid envelope, so that they can return their completed questionnaires. The PIS will inform patients of all study procedures.

Participants (both ambulance staff members and patients) will be offered the option of having a chat with one of the researchers, so that they can discuss the study and ask any possible questions they may have.

Participants will also have the opportunity to express their interest (as part of completing the questionnaires) in having an interview at a later date with one of the research team members. Following this, a member of the research team will contact potential participants by telephone to verify study eligibility, and answer any questions the participants may have. Once verbal consent has been received from participants, the researchers will schedule a face-to-face or telephone interview, including obtaining written informed consent.

Under the General Data Protection Regulation (GDPR), East Midlands Ambulance Service NHS Trust (EMAS) is the Data Controller for any personal information it processes. When EMAS shares patient information for research purposes, they ask for patient consent before doing so. Even if patients do consent, they are allowed to withdraw this consent at any time if they change their mind. EMAS always removes any information that may identify patients if it is not necessary. Accordingly, statistical information, requiring anonymised data, will always be used whenever possible.

If needed, the usual EMAS interpreter and translator services will be available to assist with discussion of the trial, the participant information sheets, and consent forms, but the consent forms and information sheets will not be available printed in other languages.

It will be explained to the potential participant that entry into the trial is entirely voluntary and that their treatment and care will not be affected by their decision. It will also be explained that they can withdraw at any time but attempts will be made to avoid this occurrence. In the event of their withdrawal it will be explained that their data collected so far may not be erased in accordance with the University’s Research Privacy Notice and information given in the Participant Information Sheet and we will seek consent to use the data in the final analyses where appropriate.

### Participant Payment

Participants will not be paid to participate in the intervention. All data collection is to occur online or in the homes of patients or via telephone, hence, no visits in excess of usual care are expected.

## CONSENT

All participants shall provide written informed consent. The ICF will be signed and dated by the participant before they enter the study.

Ambulance staff members completing the online questionnaires will consent online, prior to being able to access the questionnaire. Patients will be sent consent forms by post as part of their study packs and they will need to return their signed consent forms via a pre-paid envelope.

For participants wishing to have an interview, a member of the research team will obtain written informed consent prior to the interview taking place.

The process for obtaining participant informed consent or assent will be in accordance with the REC guidance, and Good Clinical Practice (GCP) and any other regulatory requirements that might be introduced. The investigator or their nominee and the participant or other legally authorised representative shall both sign and date the Informed Consent Form before the person can participate in the study.

One copy of the ICF will be kept by the participant and one will be kept by the Investigator.

Should there be any subsequent amendment to the final protocol, which might affect a participant’s participation in the trial, continuing consent will be obtained using an amended Consent form which will be signed by the participant.

**STUDY PROCEDURES/REGIMEN**

**STUDY FLOWCHART**

Recruitment

Pre-award

Figure 1. Schematic overview of the study.

**RANDOMISATION AND BLINDING**

This study will not involve randomisation or blinding of participants or study personnel.

**STUDY REGIMEN**

The ‘Hypo’s can strike twice’ intervention was delivered in successive county areas of East Midlands Ambulance Service NHS Trust (EMAS).

**Effectiveness of the intervention**

We will measure the effect of ‘Hypos can strike twice’ intervention on repeat ambulance calls and transportation to the hospital Emergency Departments. We will use routine anonymised data from routine call-and-dispatch and clinical records data from EMAS for 12 months before the intervention was first introduced (September 2017) to at least 6 months after the final step of the introduction in April 2019, i.e. October 2019. Dispatch data will be linked with clinical data using a unique job number. People included will be identified and tracked for repeat attendances and referrals to an appropriate healthcare professional (e.g. GP, nurse); our primary outcome will be the proportion of repeat ambulance calls and attendances for hypoglycaemia within 14 days. Repeat ambulance calls and attendance for hypoglycaemia within 30 and 90 days will be a secondary outcome.

**Cost-effectiveness of the intervention**

We will use a cost-consequences model, estimating costs from NHS Reference Costs to evaluate the costs of the intervention in relation to its effects. Total costs associated with repeat hypoglycaemic episodes will be estimated, from an NHS perspective, using unit costs from NHS Reference Costs, Emergency Services Reference Costs, and other relevant costs, multiplied by resource units.

**Process evaluation**

We will conduct a process evaluation using surveys and interviews of ambulance staff and patients to explore how ‘Hypo’s can strike twice’ exerts its effects and can be scaled up, if effective, by understanding implementation, mechanisms of impact, and contextual factors.

*Survey*

We will use a self-administered survey to understand implementation, mechanisms of impact, and contextual factors. We will use random sampling to select patients with hypoglycaemia who were attended, stratified by geographical area, from the ambulance service user records and we will send them questionnaires by post (with a stamped addressed envelope for return to the University of Lincoln) or offer them the option to complete the questionnaire on-line, according to their preference. We will conduct an online survey to all front-line clinicians to assess attitudes, perceptions and behaviour towards the intervention including the booklet. We will also conduct a self-administered postal questionnaire to patients using a Patient Reported Experience Measure^19 20^. We will survey all front-line staff and approximately 447 patients.

We will analyse the overall experience of both patients and ambulance staff, as well as use descriptive statistics and comparisons between responder groups (e.g. ambulance staff vs patients; paramedics vs emergency medical technicians), where appropriate.

